### Sample size calculation

Based on our prior experience and literature search of a 40% incidence of pAKI in this population encompassing both open and endovascular approaches of descending aortic aneurysm repairs [1, 18, 19], we expect 40% patients to develop pAKI and 60% of patients to not develop pAKI. We project that more than 70% of patients with a positive BSI to develop pAKI, while only 30% of those with a negative BSI to actually develop pAKI. From this assumption, if we recruit 80 patients to the study, we will have 32 patients expected to have pAKI (positive BSI) and 48 patients expected not to have pAKI (negative BSI). Using Fisher’s Exact Test with a 5% two-sided significance level, we will have minimum 90% power to detect the difference between 69% pAKI in patient group who will eventually develop pAKI (positive BSI) and 30% pAKI in patients who will not eventually develop pAKI (negative BSI), when sample sizes are 32 and 48, respectively. In addition, we will recruit 15 healthy group of participants to explore the feasibility of the SWE protocol, and to establish reference values on a sample of our population in terms of renal cortical stiffness, and renal parenchymal and vascular indices.

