### Statistical analyses

The analysis plan will include comprehensive graphical and statistical descriptions of the data. Baseline demographics, biomarkers, stratified by pAKI status will be summarized using descriptive summary statistics. Continuous variables will be summarized overall and within each group with the total numbers of observations, means with 95% confidence intervals, standard deviations and ranges. The two-sample t-test will be employed to compare the mean of continuous outcome variables while the Wilcoxon rank-sum test will be used for study outcomes that do not meet the normality assumption after performing appropriate data transformations. Categorical variables will be summarized overall and within each group with the total numbers of observations and percentages with exact 95% confidence intervals. To assess the accuracy and concordance of each marker with the pAKI status, we will calculate sensitivity and specificity. We will evaluate concordance (sensitivity and specificity) between pAKI status and SWE, uCCA, uNGAL alone and in combination. The BSI accuracy in predicting pAKI status will be evaluated in this study. To investigate the prognostic utility of bio-sonographic index for prediction of pAKI status, we will compare the sensitivity and specificity, using the 10% change from baseline to any of the 6 and 24 hour postoperative values alone as well as combined score (range: 0–3). Receiver operating curve (ROC) will be constructed for comparison between individual and combined components of SWE, uCCA, and uNGAL, and the differences in areas under the curve (AUC) will be assessed using a critical “z” ratio proposed by Hanley and McNeil. Intra-subject variability will be examined by comparing difference of individual readings from the median YM for each subject. The diagnostic performance of SWE and combination of each for distinguishing normal renal parenchyma from renal parenchyma affected by AKI will be assessed using a univariate logistic regression model to construct receiver operating characteristic (ROC) curves. ROC analyses will be performed to determine a cut-off point of SWE that would correctly classify the maximum number of participants based on sensitivity and specificity values. Wald asymptotic 95% confidence limits will be presented for sensitivity and specificity values. Percentile method 95% confidence intervals for ROC curves will be generated using the pROC package in R version 3.0.2 (Vienna, Austria) [28, 29]. Comparisons of area under the curves will be performed by use of a contrast matrix to take differences of the area under the empirical ROC curves. Pearson correlation coefficients will be used to assess the strength of association between continuous exposure variables. Stratified analysis of the control and AKI groups will be performed to evaluate for potential significant confounders of SWE values. SAS version 9.4 (Cary, NC) will be used for all other non-ROC related statistical analysis. Two-tailed p values of less than 0.05 will be deemed statistically significant.

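### With about 32 AKI and 48 non-AKI patients, the Wald limits fixed for sensitivity and specificity are unreliable near 0% or 100%; exact limits, already used in the same section, would avoid this

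*Protocol article*

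**What the plan says.** The Statistical analyses section of the protocol article fixes the interval method for the accuracy results: "Wald asymptotic 95% confidence limits will be presented for sensitivity and specificity values". For other proportions it uses a different method: "Categorical variables will be summarized overall and within each group with the total numbers of observations and percentages with exact 95% confidence intervals".

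The expected denominators come from Sample size calculation: "we expect 40% patients to develop pAKI and 60% of patients to not develop pAKI". With 80 patients, "we will have 32 patients expected to have pAKI (positive BSI) and 48 patients expected not to have pAKI (negative BSI". The section attaches these two counts to both AKI status and BSI status. For sensitivity and specificity the AKI-status meaning applies: 40% of 80 = 32 and 60% of 80 = 48.

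Under Procedures, Table 1 and its footnote score each of three components (shear wave elastography, cell cycle arrest markers, NGAL) as positive on a rise of at least 10% from baseline at 6 or 24 hours. The BSI is abnormal when the score is 1 or more. No expected sensitivity or specificity and no precision target is stated.

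**The concern.** A sensitivity is a binomial proportion, just like the percentages that receive exact intervals. The Wald interval takes its standard error from the observed proportion, so the interval shrinks as that proportion nears 0 or 1 and vanishes at the boundary. With denominators of 32 and 48, a strong result could be reported with an upper limit above 100%, or with no uncertainty at all. The plan hypothesizes a sensitive index, so high sensitivity is the result it hopes for, and that is where the method is weakest. The Discussion says the data will lead on to a validating trial, so overstated precision could be carried forward.

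**Working it through.** **The plan's own figure.** The power statement reads "Using Fisher’s Exact Test with a 5% two-sided significance level, we will have minimum 90% power" for 69% against 30% with 32 and 48 patients. Full enumeration of Fisher's test gives 92.8%, and the continuity-corrected normal formula gives 91.0%. The statement is reproduced and does not depend on the interval method.

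**Accuracy values implied by the projections.** The plan gives none, so I assume 40% BSI-positive, as in Table 1.
- 69% / 30% (power statement): AKI = 0.4×0.69 + 0.6×0.30 = 0.456. Sensitivity = 0.276/0.456 = 0.605. Specificity = 0.6×0.70/0.544 = 0.772.
- 90% / 30% (Table 1): AKI = 0.36 + 0.18 = 0.54. Sensitivity = 0.36/0.54 = 0.667. Specificity = 0.42/0.46 = 0.913.

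**Coverage.** The Wald interval is x/n ± 1.96·√[(x/n)(1 − x/n)/n]. Its actual coverage at a true value p is the sum of the binomial probabilities of every x whose interval contains p.

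| True value | Wald, n=32 | Wald, n=48 |
|---|---|---|
| 0.605 | 95.4% | 94.6% |
| 0.667 | 92.9% | 93.2% |
| 0.772 | 93.6% | 92.8% |
| 0.80 | 89.0% | 92.9% |
| 0.85 | 86.3% | 93.4% |
| 0.90 | 84.0% | 86.4% |
| 0.91 | 94.5% | 92.8% |
| 0.95 | 80.2% | 91.2% |
| 0.98 | 47.6% | 62.0% |

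Coverage at 1 − p is the same, so low specificities suffer equally. Because coverage oscillates, averages are fairer than single points. Over 0.60-0.80 the mean is 92.9% (n=32) and 93.7% (n=48); over 0.90-0.95 it is 87.4% and 89.8%. At the implied values, taking sensitivity at n=32 and specificity at n=48, coverage is 95.4% and 92.8% (69%/30%) or 92.9% and 92.2% (Table 1, with specificity 0.913).

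**Dependence on the assumption.** If AKI is instead held at 40%, the BSI-positive share is (0.40 − 0.30)/(0.69 − 0.30) = 0.256. Sensitivity is then 0.69×0.256/0.40 = 0.442 and specificity 0.70×0.744/0.60 = 0.868, with coverage 92.4% and 88.6%. With 90%/30% the share is 0.10/0.60 = 0.167, specificity is 0.70×0.833/0.60 = 0.972, and coverage at n=48 is 74.2%.

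**Limits above 100%.** The upper limit passes 1 when n − x < 3.84·x/n and x < n, that is, with 1, 2 or 3 misses at either sample size. At a true value of 0.90 the chance of this is 57% (n=32) or 27% (n=48); at 0.70 it is about 0.5% or less.

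**Examples.** For 29/32, p = 0.906, standard error = √(0.906×0.094/32) = 0.0515, half-width = 0.101.

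| Observed | Wald | Wilson | Exact |
|---|---|---|---|
| 22/32 | 52.7-84.8% | 51.4-82.0% | 50.0-83.9% |
| 29/32 | 80.5-100.7% | 75.8-96.8% | 75.0-98.0% |
| 32/32 | 100-100% | 89.3-100% | 89.1-100% |
| 45/48 | 86.9-100.6% | 83.2-97.9% | 82.8-98.7% |
| 48/48 | 100-100% | 92.6-100% | 92.6-100% |

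**Mean width, n=32.** At 0.70: Wald 0.311, Wilson 0.298, exact 0.330. At 0.95: 0.130, 0.166, 0.179. Below about 0.85 Wald is slightly wider than Wilson, so its mid-range fault is that it is off-centre.

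**Plausibility of extreme values.** As an illustration with three independent components of equal sensitivity c, the BSI sensitivity is 1 − (1 − c)³: 0.875 for c = 0.5 and 0.973 for c = 0.7. Positive correlation between components would weaken this. The same rule lowers specificity.

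**The case against.** The strongest objection is one of breadth. The damage depends on the true accuracy, for which the plan states no figure. At the values implied by its projections with 40% BSI-positive, the shortfall is at most about 3 points. Individual low points such as 0.90 also sit beside much better neighbours such as 0.91. A reader might infer that Wald limits at 32 and 48 patients always under-cover badly and are always too narrow. The documents do not support that: the serious deficit is near the boundary, and in the mid-range Wald intervals are slightly wider than Wilson intervals. This part of the objection stands and sets the limits of the point.

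Nor does anything inferential depend on these limits. The sample size rests on Fisher's test, markers are compared through areas under the curve, no decision rule uses the intervals, and the study calls itself exploratory. That also stands. A reader who infers that power or the main test is compromised would be wrong.

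Finally, the Wald sentence follows directly on the sentence about the elastography cut-off, so it may have been meant only for that. The wording carries no such restriction, and the section reports sensitivity and specificity for each marker and for the combination. On the narrower reading the point still applies to the elastography results, and the method for the BSI would need to be stated.

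**Conclusion.** The point holds as a reporting weakness confined to proportions near 0 or 1. With 32 patients, coverage of the nominal 95% interval is 84% at 0.90, 80% at 0.95 and 48% at 0.98; with 48 it is 86%, 91% and 62%, with oscillation between these points. Impossible upper limits arise with one to three misses, and zero width with none. In the mid-range the loss is small, about 92-95% coverage at the values implied by the projections.

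Two assumptions matter. The mid-range figure takes 40% of patients as BSI-positive; holding AKI at 40% instead moves the implied specificity to 0.87-0.97, where coverage is worse. The denominators of 32 and 48 are expectations only. The any-one-of-three rule makes near-boundary results plausible but does not establish that they will occur.

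**What to change.** In Statistical analyses, replace the Wald asymptotic limits with exact (Clopper-Pearson) 95% limits for all sensitivities and specificities, single markers and combinations alike. This matches the method that the section already names for percentages. Wilson score limits are an acceptable alternative. Neither exceeds 100%. Exact coverage is at least 95% throughout, and Wilson coverage averages about 95% over true values of 0.50-0.90 (lowest 92.3%).

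The cost is a change of wording and a software option. Exact intervals are somewhat wider throughout (at n=32 and a true value of 0.70, mean width 0.330 against 0.311). Wilson intervals are wider only near the boundary and slightly narrower in the mid-range. No patients, measurements or tests change.

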### Procedures

The bio-sonographic index (BSI) will be performed on the study patients at baseline- during their preoperative visit, and at 6 hours and at 24 hours after the procedure. The BSI will be composed of SWE, urinary cell cycle arrest (uCCA) and urinary NGAL (uNGAL). Abnormal BSI will be diagnosed as an increase of at least 10% from baseline to any of the 6 and 24 hour time points. Based on an estimated incidence of pAKI of 40% in this population, a probability of abnormal BSI will be estimated as follows (Table 1).

**Table 1 pone.0241782.t001:** The BSI criteria.

AKI	combination	SWE (YM)	uCCA	uNGAL	Patients	AKI %
Y	Abnormal	≥10% = 1, < 10% = 0	≥10% = 1 < 10% = 0	≥10% = 1 < 10% = 0	40%	90%
N	Normal	SWE <10% = 0	< 10% = 0	< 10% = 0	60%	30%

* Values are in reference to a change from baseline to any of time points 2, and 3.

AKI (Y/N) = YM based on SWE & urine biomarkers

AKI: acute kidney injury; SWE: shear wave elastography; YM; Yong Elastic Module; uCCA: urinary cell cycle arrest; uNGAL, urinary neutrophil gelatinase-associated lipocalin; Y: yes; N: no; BSI: biosonographic index; BSI score is the sum of SWE, Biomarker, and NGAL. It is abnormal if ≥ 1. Total score can range from 0 to 3.

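### Two procedures are named for AUC differences without saying which governs where they overlap, and one of them, in its usual form, is conservative for the 0/1 components and the 0-3 BSI score

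*Protocol article*

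**What the plan says.** All statements on the tests are in the protocol article, Statistical analyses.

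- First procedure, tied to ROC curves for the three markers taken singly and together: "the differences in areas under the curve (AUC) will be assessed using a critical “z” ratio proposed by Hanley and McNeil".
- Second procedure, several sentences later, after the text on logistic-regression ROC curves, the SWE cut-off and the R package for ROC intervals: "Comparisons of area under the curves will be performed by use of a contrast matrix". The contrast is applied to empirical areas, and no scope is attached to it.
- Neither procedure is called primary, secondary or a sensitivity analysis. The section applies a two-tailed 0.05 criterion throughout.

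The scale of the score is set under Procedures, in the notes to Table 1: "BSI score is the sum of SWE, Biomarker, and NGAL. It is abnormal if ≥ 1. Total score can range from 0 to 3". Statistical analyses repeats the range when it speaks of "values alone as well as combined score (range: 0–3"). Each component is scored 1 for a rise of at least 10% from baseline and 0 otherwise. All markers are measured in the same 80 patients.

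**The concern.** The abstract lists a comparison of individual with combined BSI components among the planned analyses, and the point of a combined index is that it should do better than its parts. For that comparison the text fixes two tests and gives no rule for choosing between them.

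The two are not interchangeable on this scale. The exponential-formula standard error usually paired with the Hanley-McNeil z depends only on the AUC and the two group sizes, so it takes no account of ties. With a 0/1 marker, or a score with four values, ties are very common, and the formula then overstates the standard error. The contrast of empirical areas estimates its variance from the data, ties included. At stake are some of the power to show that the index adds anything to a single component, and clarity about which p-value is reported.

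**Working it through.** **The plan's own figure.** The only power figure in the article is for Fisher's exact test: 69% against 30%, groups of 32 and 48, two-sided 5%, at least 90% power. Exact enumeration gives 92.8%, so the statement holds. It says nothing about AUC comparisons; no power is given for those.

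**Step 1: standard error for a 0/1 marker.** Group sizes of 32 and 48 come from Sample size calculation. Sensitivity and specificity of 0.6 are assumed, so AUC = A = (0.6 + 0.6)/2 = 0.6.

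Exponential formula: Q1 = A/(2 − A) = 0.4286 and Q2 = 2A²/(1 + A) = 0.45.

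Var = [A(1 − A) + 31(Q1 − A²) + 47(Q2 − A²)]/(32 × 48) = [0.24 + 31 × 0.0686 + 47 × 0.09]/1536 = 6.596/1536 = 0.00429, so SE = 0.066.

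Empirical: Var = ¼[0.24/32 + 0.24/48] = 0.003125, so SE = 0.056.

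The exponential formula is too large by a factor of 0.066/0.056, about 1.18.

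**Step 2: effect on the paired test.** Both tests use z = (A₁ − A₂)/√(SE₁² + SE₂² − 2r·SE₁·SE₂) or its empirical equivalent. Simulated data had 32 pAKI and 48 non-pAKI patients and three correlated normal markers (correlation 0.1, 0.3 or 0.5), cut to 0/1 and summed to 0-3. There were 1,500 to 3,000 data sets per scenario. The score's AUC was tested against that of one component. The contrast was given the DeLong covariance. Hanley-McNeil was run with the exponential or a nonparametric SE, and with Pearson or Kendall correlation between markers. Its area-correlation table is not in the article and was rebuilt under a binormal model.

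No marker informative (true AUCs equal): type I error was 4.3-4.8% for the empirical contrast and 1.4-2.7% for Hanley-McNeil with the exponential SE.

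One scenario with a real difference (shift 0.8 SD per marker, correlation 0.3, cut at 0.3 SD; AUC 0.74 for the score and 0.66 for the component):

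| Test | Rejects | Disagrees with contrast |
|---|---|---|
| Empirical contrast | 50% | – |
| Hanley-McNeil, exponential SE, Pearson | 40% | 10% |
| Hanley-McNeil, exponential SE, Kendall | 34% | 16% |
| Hanley-McNeil, nonparametric SE, Pearson | 49% | 2% |
| Hanley-McNeil, nonparametric SE, Kendall | 44% | 7% |

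**Step 3: how far this depends on assumptions.** Disagreement means falling on opposite sides of two-sided 0.05. Over all tied scenarios with a real AUC difference it was about:

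- exponential SE: 6-31% (Pearson), 10-36% (Kendall);
- nonparametric SE: 1-5% (Pearson), 3-10% (Kendall).

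For untied sums against a continuous marker it was about 2-5% with Pearson and 9-24% with Kendall. With no AUC difference, tied scores gave about 0.4-3%.

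**Step 4: would choosing the better p-value inflate false positives?** The chance that at least one test rejects is (a + b + d)/2, where a and b are the rejection rates and d is the disagreement. With no marker informative, exponential SE and Pearson:

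- correlation 0.1: (4.8 + 2.7 + 2.1)/2 = 4.8%;
- correlation 0.3: (4.3 + 2.7 + 1.6)/2 = 4.3%.

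These equal the empirical contrast's own rates, so the choice adds practically nothing under the null.

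**The case against.** **Separate purposes.** The Hanley-McNeil sentence concerns individual against combined components, while the contrast sentence follows text on SWE, logistic regression and cut-offs, so two scopes may have been intended. That is possible but not stated. The intervening text itself covers SWE and combinations, so SWE against a combination falls under both sentences. This is also not detail left to an analysis plan: the article states two methods rather than leaving the method open.

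**Continuous markers.** The ROC sentence does not say that the components enter as 0/1, and seeking an SWE cut-off implies that SWE is continuous there. This stands. With continuous markers and Pearson correlation the two tests mostly agree, so the loss from ties is conditional. Nor are ties the only source of disagreement, as the Kendall results for untied data show.

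**Stronger readings a reader might infer.** One is that the tests differ often enough to change the study's conclusion. The documents do not support this: disagreement runs from under 1% to about 36% depending on choices the article does not make, and no success criterion rests on an AUC difference. Another is that pairing would be ignored, at a large cost in power; nothing in the text says so. A third is that selective reporting would inflate false positives; Step 4 shows practically no inflation for the exponential-formula version.

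**Stakes.** The sample size rests on Fisher's test of pAKI by BSI status, and the Discussion calls the study exploratory. Both points stand and limit the weight of the finding.

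**Conclusion.** The conflict in the text is certain: two procedures are named for AUC differences, their scopes overlap, and nothing says which governs.

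Its numerical effect is conditional. If Hanley-McNeil is applied with the exponential-formula SE to the 0/1 components and the 0-3 score, type I error is about 1.4-2.7% instead of 4.3-4.8%. Power in the worked scenario falls by 10 to 16 points (from 50% to 40% or 34%). With a nonparametric SE, or with continuous markers and Pearson correlation, the tests mostly agree. What may change is the significance of a single AUC comparison, not the result on which the study is sized.

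The figures rest on assumed marker shifts, correlations and cut-offs, on a rebuilt area-correlation table, and on reading the contrast matrix as a DeLong contrast, which the article does not name. The point should be corrected, chiefly because the correction is almost free.

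**What to change.** Delete the clause on the Hanley-McNeil z ratio. State one method for all AUC comparisons: the paired contrast of empirical ROC areas in the same patients (for example with the DeLong covariance), for BSI against each of SWE, uCCA and uNGAL, reporting each AUC difference with its 95% CI. In the same sentence, say whether the components enter as 0/1 indicators or as continuous values.

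The cost is one sentence. Sample size, data collection and study procedures do not change, and the plan already names a contrast of empirical areas.

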
### Intra- and interobserver reliability

Intra- and inter-observer values/data will be evaluated for repeatability (between subjects) and reproducibility (between readers). Average values of will be quantified and Bland–Altman analysis will be performed to assess the repeatability of the techniques, while the Friedman test will be used to assess reproducibility.

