### Participants

A total of 80 patients for the ‘study group’ will be enrolled. Each patient will serve as his/her own control by studying the change in BSI from preoperative values to 6 and 24 hr after the procedure. A total of 15 normal healthy volunteers will be enrolled as a ‘feasibility group’ to test the feasibility of the SWE protocol.

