#### Shear wave elastography exam

The ultrasonographic examination of the kidney will be performed using the Mindray Rosana 7 system (Mindray North America, CA, USA) equipped by the SC6-1u transducer for acquiring grayscale, spectral Doppler, and virtual touch tissue quantification on acoustic radiation force impulse (ARFI) imaging in the healthy adults. The exam will be performed by a certified radiology technician with over 10 years of experience and read by an independent radiologist who is blinded to the study protocol. We will use the SWE published and outlined by Sandhu et al. [20] as follows: During each encounter, both kidneys will be evaluated. The flank approach will be used to access both kidneys to minimize dissipation of U/S waves by distances traveled through or by pathology of the spleen and liver for the left and right kidneys, respectively. Exams will be performed in the left and right lateral decubitus positions for imaging the left and right kidney, respectively. Before scanning, we will adjust the image acquisition settings as follows: MI 1.4, image depth 10–12 cm, scanning frequency 3.5 MHz, single focus, dynamic range 65, harmonic imaging, Map E/Space-time 2, and total gain 0–1. The presence or absence of hydronephrosis, calculi, masses, and perinephric collections will be also assessed; the presence of any of these findings and will serve as exclusion criteria. For each participant, the following values will be obtained during suspended respiration: each kidney size in the longitudinal plane; main renal artery peak systolic velocity (PSV), end diastolic velocity (EDV), and resistive index (RI); inferior interlobular artery PSV, EDV, and RI; mid-interlobular artery PSV, EDV, and RI; superior interlobular artery PSV, EDV, and RI; shear-wave velocity values at the renal cortex (five measurements in the longitudinal plane at the upper, upper-mid, mid, mid-lower, and lower poles and three measurements in the transverse plane at upper, mid, and lower poles). All measurements will be repeated to yield two measurements per parameter per observer. Each patient will be scanned by a technician and by the principle investigator (AZ) on the study. Images will be interpreted independently by a radiologist and a vascular surgeon who are blind to the study protocol.

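### The Friedman test, the only method named for between-reader reproducibility of SWE, detects a systematic shift between readers but does not measure their agreement

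*Protocol article*

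**What the plan says.** The section Intra- and interobserver reliability of the protocol article separates two properties: "Intra- and inter-observer values/data will be evaluated for repeatability (between subjects) and reproducibility (between readers"). It then gives each its own method. For the first, "Bland–Altman analysis will be performed to assess the repeatability of the techniques"; for the second, "while the Friedman test will be used to assess reproducibility". No other between-reader statistic is named in the article. Statistical analyses also mentions intra-subject variability, examined as the distance of single readings from the subject's median Young's modulus, but that does not concern readers.

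The design is described under Shear wave elastography exam. There are two operators: "Each patient will be scanned by a technician and by the principle investigator". There are two readers: "Images will be interpreted independently by a radiologist and a vascular surgeon". There are duplicates: "All measurements will be repeated to yield two measurements per parameter per observer". Under Participants, "A total of 80 patients for the ‘study group’ will be enrolled", together with 15 healthy volunteers who serve to test the feasibility of the SWE protocol.

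**The concern.** Reproducibility between readers is a question of agreement: how far apart are two readings of the same kidney? The Friedman test ranks the readers within each subject and asks whether one tends to rank higher than another. Its null hypothesis is the absence of a systematic location difference. A non-significant result is therefore no evidence of agreement, a significant one may reflect a trivial constant offset, and neither states an error size.

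The error size is what this study needs. Under Procedures and Table 1, a rise of at least 10% from baseline in any single component, at 6 or 24 hours, makes the bio-sonographic index abnormal. Random error in SWE feeds directly into that classification. If one reader reads all three examinations of a patient, a constant proportional offset cancels from the percent change, whereas random error does not. The test named is sensitive to the part that can cancel and blind to the part that cannot.

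There is also a wording fault. Repeatability is labelled as a between-subject property. The duplicates collected are within subject and within observer; spread between subjects is not measurement error.

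**Working it through.** The reliability section states no figure, so there is none to reproduce. The check is of how the named test behaves in this design.

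**Inputs from the protocol article.** Two readers (or 2 × 2 = 4 operator-by-reader combinations); n = 80 patients, n = 15 volunteers; two-sided alpha 0.05. **Assumed**, because no SDs are given: normal between-subject variation and reader error, with the sizes shown below.

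**Step 1: exact result for two readers.** With k = 2 the Friedman statistic reduces to a sign test. If B is the number of subjects in whom reader 2 reads higher than reader 1, then Q = (2B − n)²/n, referred to chi-square with 1 df (critical value 3.84).

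- n = 80: B = 49 gives (98 − 80)²/80 = 4.05, so the test rejects when B ≥ 49 or B ≤ 31.
- n = 15: it rejects when B ≥ 12 or B ≤ 3.

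B is binomial with p = Φ(δ / (√2·σe)), where δ is the constant shift and σe the error SD per reader.

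- *No shift* (δ = 0): p = 0.5 whatever σe is. Rejection is 5.7% at n = 80 and 3.5% at n = 15.
- *Shift of 0.1 between-subject SD, σe = 0.1 between-subject SD*: p = Φ(0.1/0.1414) = 0.760. Rejection is 99.9% at n = 80 and about 50% at n = 15.

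**Step 2: agreement in the same settings** (between-subject variance set to 1).

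- No shift, σe = 1: ICC = 1/(1 + 1) = 0.50. These readers pass in about 94% of studies of 80.
- Shift 0.1, σe = 0.1: the two reader means contribute variance 0.1²/2 = 0.005, so the absolute-agreement ICC = 1/(1 + 0.005 + 0.01) = 0.985. These readers almost always fail.

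**Step 3: simulation over wider settings**, 4,000 replicates each, n = 80, between-subject SD 2 units except in the first row, where the readers share no signal.

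| Readers | Mean ICC(2,1) | Rejection, k = 2 | Rejection, k = 4 |
|---|---|---|---|
| Unrelated, no shift | 0.00 | 5.6% | 5.0% |
| Poor (error SD 4), no shift | 0.20 | 5.6% | 5.0% |
| Near-perfect (error SD 0.1), no shift | 0.997 | 6.1% | 4.6% |
| Near-perfect (error SD 0.1), shift 0.1 | 0.996–0.997 | 100% | 100% |

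The test cannot tell the first three rows apart; the ICC separates them clearly. At n = 15 the last row falls to 49.6% (k = 2) and 50.2% (k = 4).

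**Step 4: why an error size is needed.** Suppose there is no true change and independent log-normal error at each examination. A false SWE-positive occurs when max(e6, e24) − e0 ≥ ln 1.10. With a measurement CV of 5% this happens in about 15% of patients; with a CV of 10%, in about 38%. These CVs are illustrative. The plan must estimate the real one, and the Friedman test returns nothing that can be set against the 10% threshold.

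**The case against.** Five things can be said for the plan.

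- **No decision rule is written.** The protocol does not say that a non-significant Friedman result will be read as reproducible, or a significant one as the reverse. That is correct, and a test for systematic reader shift is a legitimate part of a reproducibility assessment. But with no other between-reader method named, the p-value is all the reader of the results would have.
- **Bland–Altman analysis is already planned** and will give an error estimate for repeatability. That is also true, and it makes part of the proposed repeatability reporting a refinement. It leaves the between-reader gap: the sentence sets Bland–Altman against Friedman and assigns only the latter to readers.
- **Feasibility rests on the 15 volunteers**, where near-perfect readers with a small shift would fail about half the time, not almost always. This stands as a limit on the 99.9% figure, which is for 80 patients. It does not help in the other direction: with 15 subjects, unrelated readers still pass in about 97% of studies.
- **The study calls itself exploratory, and this is a supporting analysis.** The AKI outcome and the accuracy analysis of the index are unaffected, which limits the weight of the point.
- **The article is condensed and no SAP is shown.** Missing detail would not be a finding, and one sentence in the section has lost its object. Here, however, the article names a method, and that method does not answer the question it is given.

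**Conclusion.** The concern holds. As the only method named for between-reader reproducibility, the Friedman test cannot show agreement and gives no between-reader error. With two readers and 80 patients it rejects in 5.7% of studies when there is no shift, even if the readers share no signal. It rejects in 99.9% when readers with an absolute-agreement ICC of about 0.985 differ by a constant 0.1 between-subject SD. The first figure is free of distributional size assumptions; it needs only symmetric, independent reader errors. The second rests on the assumed shift and error SD, and falls to about 50% with 15 subjects. The between-subject label on repeatability is a separate, smaller wording error. The point should be corrected, but it does not threaten the primary analysis.

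**What to change.** In Intra- and interobserver reliability:

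1. **Reproducibility.** Use a two-way random-effects, absolute-agreement ICC with 95% CI, plus Bland–Altman bias and limits of agreement between operators and between readers. The Friedman test may stay as a supplementary check for systematic shift.
2. **Repeatability.** Report the within-subject SD and repeatability coefficient of the duplicate measurements, on the log scale so that they read as percentages, and compare them with the 10% threshold. This makes explicit what the planned Bland–Altman analysis of the duplicates would largely supply.
3. **Definition.** Replace the between-subjects label on repeatability with within subject, within observer.

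The cost is wording only. The duplicate measurements, two operators and two readers are already in the imaging protocol, so no extra scans or patients are needed.
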